## Abstract

**Background:**

Low back pain is a relevant public health problem, being an important cause of work absenteeism worldwide, as well as affecting the quality of life of sufferers and their individual functional performances. Supervised active physical routines and of cognitive-behavioral therapies are recommended for the treatment of chronic Low back pain, although evidence to support the effectiveness of different techniques is missing. Accordingly, the aim of this study is to contrast the effectiveness of two types of exercises, graded activity or supervised, in decreasing symptoms of chronic low back pain.

**Methods/design:**

Sample will consist of 66 patients, blindly allocated into one of two groups: 1) Graded activity which, based on an operant approach, will use time-contingent methods aiming to increase participants’ activity levels; 2) Supervised exercise, where participants will be trained for strengthening, stretching, and motor control targeting different muscle groups. Interventions will last one hour, and will happen twice a week for 6 weeks. Outcomes (pain, disability, quality of life, global perceived effect, return to work, physical activity, physical capacity, and kinesiophobia) will be assessed at baseline, at treatment end, and three and six months after treatment end. Data collection will be conducted by an investigator blinded to treatment allocation.

**Discussion:**

This project describes the randomisation method that will be used to compare the effectiveness of two different treatments for chronic low back pain: graded activity and supervised exercises. Since optimal approach for patients with chronic back pain have yet not been defined based on evidence, good quality studies on the subject are necessary.

**Trial registration:**

NCT01719276

## Background

Low back pain (LBP) is a relevant public health problem, being an important cause of work absenteeism worldwide [1-3], as well as affecting sufferers’ quality of life [1] and individual functional performances [1]. Non-specific chronic LBP (cLBP), which does not have a well-defined etiology and presents pain for at least 12 consecutive weeks, represents up to 95% of the cases of LBP [1]. The annual direct costs of cLBP in the United States range from 12.2 to 90.6 billions of dollars, and represent only 14.5% of the total costs of this health condition [4]. Life-time prevalence of cLBP ranges from 11 to 84%; 1-year prevalence ranges from 22% to 65%, and point-prevalence from 12% to 33% [5].

The European Guidelines recommends the use of supervised active exercises, manipulation/mobilization, Back Schools, multidisciplinary approaches and cognitive-behavioral therapies for patients with cLBP [1]. Evidence suggests that supervised exercise and cognitive behavioral therapies improve pain and reduce functional disability [6].

Strengthening exercises for abdominal and trunk muscles, motor control exercises for lumbar multifidus (LM) and transversus abdominis (TrA) and stretching exercises for trunk and lower limbs show some evidence of improvement of pain and functional disability in individuals with cLBP [1,7,8]. Strengthening exercises of abdominal and trunk muscles are based on the known association between weakness of the trunk and abdomen muscles and low back pain [9-14]. Weakness is a consequence of sedentary life, and is associated to paravertebral muscle hypotrophy [14] and changes in motor control [15]. Furthermore, deep muscles of the abdomen and trunk such as the TrA and LM are also affected in patients with cLBP [16]. Some studies have focused on the individual use of muscle stretching and strengthening or motor control in cLBP [17,18]. However, Macedo and colleagues [19], on their systematic review, recommend motor control exercises associated with other types of exercise.

Cognitive behavioral therapy uses brief interventions and counseling strategies in order to facilitate behavioral changes [20], by modifying negative attitudes and beliefs [21]. The “Back Book” [22] may be used as a good educational support, since it offers evidence-based information that is consistent with biopsychosocial models. Cognitive-behavioral programs that showed some evidence for use in patients with cLBP include the Back Skills Training program (BeST) [21,23], Brief Intervention (BI) [24,25] and the Graded Activity [26].

The Graded Activity program, which was initially developed by Lindstrõm *et al.*[27], recommends the use of an individualized and submaximal exercise program, with educational support in order to enhance self-trust and tolerance to effort. Although it has been suggested that graded activity is effective in decreasing pain and functional disability in cLBP [26,28], van der Giessen (2012), in a systematic review [29], concluded that there is insufficient evidence on the effects of graded activity in pain, disability and return to work in patients with non-specific cLBP. Furthermore, the *Clinical Practice Guidelines Linked to the International Classification of Functioning*, *Disability*, *and Health from the Orthopaedic Section of the American Physical Therapy Association*[3] states that effectiveness of cognitive behavioral therapy in cLBP is moderate.

The literature is not clear regarding which exercise programs are most effective for patients with cLBP; therefore, more randomised controlled trials are necessary to clarify these questions. Moreover, little is known about the effect of graded activity compared with supervised exercise program (strengthening, stretching and motor control) in patients with non-specific cLBP.

### Study aim

The aim of this paper is to report the study protocol used to investigate the effect of two types of exercise program in reducing the symptoms of non-specific cLBP.

## Methods and design

The study will be a randomised controlled trial comparing graded activity with a supervised exercise program in patients with non-specific cLBP. Each treatment program will consist of 12 individually supervised 1-hour sessions over a six-week period.

### Enrollment and eligibility criteria

A total of 66 patients will be recruited at the Rehabilitation Center of Taboao da Serra, Brazil.

#### Inclusion criteria

· Non-specific cLBP;

· Age between 18 and 65 years;

· A minimum pain intensity score of three in the 11-point Pain Numerical Rating Scale [24].

#### Exclusion criteria

· Known or suspected serious spinal pathology (fractures, tumors, inflammatory or infective diseases of the spine);

· Nerve root compromise;

· Comorbid health conditions that would prevent active participation in the exercise programs;

· Pregnancy;

· Cardio-respiratory illnesses.

In order to ensure patients’ safe participation in the study, the *Physical Activity Readiness Questionnaire* (PAR-Q) will be used [30]. Those answering “yes” to any of the questions will be excluded.

### Procedures

All measurements will be conducted by a physical therapist blinded to patients’ groups. The investigator will confirm the eligibility criteria, as well as obtain demographic (civil status, education, tabagism and use of medication) and anthropometric data (age, height, weight and body mass index). Past treatments and use of medication for cLBP will also be recorded. The investigator will also assess primary (pain severity and functional disability) and secondary outcomes (quality of life, global perceived effect, return to work, physical activity, physical capacity and kinesiophobia). Patients will be assessed at baseline, immediately after the treatment and at three and six-month follow-up.

### Randomisation procedures

Before treatment onset, the patients will be randomly allocated into one of two groups: Graded Activity (GA) or Supervised Exercise (SE), through a computer-generated randomisation schedule that will be performed by an independent researcher, not involved in other study procedures. The allocation of participants will be concealed by using consecutive numbered, sealed and opaque envelopes [31]. The flow of the study is summarized in Figure 1.

**Figure 1 F1:**
[figure not shown]
Flow diagram of the study.

### Outcome measures

All instruments were used in their translated and adapted to Brazilian-Portuguese versions, with adequate psychometrical properties [24,25,32-34]. Pain, functional disability, return to work, physical activity, physical capacity and kinesiophobia will be measured.

### Primary outcomes

#### Pain

Pain will be assessed quantitatively and qualitatively with the *Numerical Rating Scale* (NRS) and the *McGill Pain Questionnaire*. The NRS is an 11-point scale ranging from 0 to 10, in which 0 defines absence of pain and 10 describes unbearable pain [24]. Participants will be asked to rate the average pain levels over the week before assessment [24].

The *McGill Pain Questionnaire* provides a multidimensional assessment of pain. It consists of 78 descriptors of the quantity and quality of pain which are grouped in four major domains (sensory, affective, evaluative and miscellanea) and 20 sub-domains with 1 to 5 descriptors each, to which intensity values are assigned. The questionnaire is used to describe pain experience and the score corresponds to the sum of the aggregated values. Maximal scores will be: Sensorial = 41, Affective = 14, Evaluative = 5, Miscellanea = 17, Total = 7 [35].

#### Functional disability

The *Roland Morris Disability Questionnaire* will be used to assess functional disability due to LBP. It consists of 24 questions focusing on normal activities of daily life. Each affirmative answer corresponds to 1 point and the final score is determined by the total number of points. Total score ranges from 0 to 24 and higher scores reflect increased disability. Scores above 14 reflect severe impairment [24,25,36].

### Secondary outcomes

#### Quality of life

*Short**Form Health Survey Questionnaire* (SF-36) assesses health-related qualify of life. It consists of 36 questions grouped in eight domains: vitality (4 items), Physical Functioning (10 items), Bodily Pain (2 items), General Health (5 items), Physical Role (2 items), Emotional Role (3 items), Social Functioning (2 items) and Mental Health (5 items). For each domain, scores range from 0 to 100 and higher scores reflect better quality of life. Only the physical and emotional domains will be used [32].

#### Global perceived effect

The *Global Perceived Effect Scale* is an 11-point scale that ranges from −5 (vastly worse), zero (no change) to +5 (completely recovered). For all of the measures of perceived global effect, the participants will be asked the following question: “Compared to when this episode first started, how would you describe your back?” Positive scores represent greater recovery and negative scores represent worsening of the symptoms [24].

#### Return to work

The evaluation will be made by questioning if the patient is off work due to back pain and the positive or negative response will be recorded.

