### Sample size calculation

Sample size was defined in order to detect a 2-point difference between groups on the pain intensity outcome measured by the *Pain Numerical Rating Scale*, assuming a standard deviation of 1.9 points [24]. We also sought power to detect a 4-point difference in functional disability measured by the *Roland Morris Disability Questionnaire*, with an estimated standard deviation of 4.9 points [24,25,36]. Power was defined as 80% for an alpha of 5% and attrition (drop-outs) of 15%. Accordingly, 33 participants per group will be needed.

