### Statistical analyses

All of the statistical analysis will be based on intention-to-treat basis [44]. We will use linear mixed models to test for treatment effects between groups at the end of the treatment and at three and six-month follow-up. Treatment effect sizes will be calculated for each time points, as well as statistical significance. Analyses will be conducted using SPSS 19 and SigmaPlot 10. A level of significance of 5% will be used.

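### The 'return to work' outcome records whether a patient is off work at a visit, and the only model named does not suit a yes/no item

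*Protocol article*

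**What the plan says.** The Procedures section of the protocol article names the "secondary outcomes (quality of life, global perceived effect, return to work, physical activity, physical capacity and kinesiophobia". It adds: "Patients will be assessed at baseline, immediately after the treatment and at three and six-month follow-up". The Return to work section gives the whole measurement in one sentence, "questioning if the patient is off work due to back pain and the positive or negative response will be recorded".

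Three other places bear on this:

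- **Inclusion criteria.** The list is non-specific chronic low back pain, "Age between 18 and 65 years", and a pain score of at least three. Neither this list nor the exclusion list mentions employment or sick leave.
- **Procedures.** The background data listed are "demographic (civil status, education, tabagism and use of medication", plus anthropometric data and past treatment. Work status is not listed.
- **Statistical analyses.** "All of the statistical analysis will be based on intention-to-treat basis", and "We will use linear mixed models to test for treatment effects between groups" at the three post-baseline times. No other model is named and no outcome is excepted.

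**The concern.** Return to work is a transition that only a patient off work at the start can make. The item records a state at each visit. Asked of all patients, a negative answer pools those who went back to work with those who never stopped, and possibly with those who have no job. New absences among patients who were working at baseline enter the same comparison.

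Two things are at stake. First, a small or null difference in off-work status could be published as a finding on return to work. The Background cites a systematic review that found insufficient evidence on graded activity for this very outcome, so the label matters. Second, a model that assumes normal errors of constant variance would be applied to a yes/no answer that may have only a handful of positive responses per arm.

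**Working it through.** The plan gives no figure for this outcome, so there is none to reproduce. The sample size section was built to "detect a 2-point difference between groups on the pain intensity outcome" and a difference in disability, and does not mention work.

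**Inputs**

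- From the article: 33 per group and 15% attrition, so 33 × 0.85 = 28 per group at follow-up.
- Assumed, because the article gives neither: the share *f* off work at baseline (10% to 30%), and the proportion *r* of those who return (60% versus 40%). No new absences are assumed.

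**Step 1: dilution on the absolute scale.** The proportion of the whole arm off work at follow-up is *f* × (1 − *r*).

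| *f* | Arm with 60% return | Arm with 40% return | Difference |
|---|---|---|---|
| 10% | 0.1 × 0.4 = 4% | 0.1 × 0.6 = 6% | 2 points |
| 20% | 0.2 × 0.4 = 8% | 0.2 × 0.6 = 12% | 4 points |
| 30% | 0.3 × 0.4 = 12% | 0.3 × 0.6 = 18% | 6 points |

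A true difference of 20 points in return is multiplied by *f*.

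**Step 2: the same figures on the ratio scale.** The risk ratio for still being off work is 0.40 / 0.60 = 0.67 among those off work at baseline, and 8% / 12% = 0.67 in the whole sample. The dilution belongs to the risk difference, which is what a linear model estimates.

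**Step 3: number of events.** At *f* = 20%, the expected number off work per arm is 33 × 0.08 = 2.6 and 33 × 0.12 = 4.0, or about 3 to 4. With 28 per arm it is 2.2 and 3.4.

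**Step 4: variance.** A binary item has variance *p*(1 − *p*). This is 0.05 × 0.95 = 0.048, 0.10 × 0.90 = 0.090 and 0.20 × 0.80 = 0.160. The variance moves with the mean, so it is not constant across arms or visits if the proportion changes.

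**Step 5: what redefinition can rescue.** The number informative per arm among 28 is 28 × *f*. For another 20-point contrast (70% versus 50% return), the usual two-proportion formula at two-sided 5% gives power = Φ[(Δ − 1.96 √(2p̄(1 − p̄)/n)) / √((p₁(1 − p₁) + p₂(1 − p₂))/n)].

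| *f* | Informative per arm | Power, off work at baseline only | Power, all patients |
|---|---|---|---|
| 10% | 2.8 | 7% | 6% |
| 20% | 5.6 | 10% | 8% |
| 30% | 8.4 | 13% | 10% |

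The formula is rough at such sizes, but the message is plain: neither version supports a test.

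**The case against.** The other side has a good deal to say, and several stronger readings that a reader might infer do not hold.

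- **That return to work cannot be obtained at all.** Outcomes are assessed at baseline too, so a change from off work to not off work can be derived, and patients who never stopped can be told apart from those who returned. This stands. What remains is that the article defines no such derivation and no denominator, and the baseline answer does not separate workers from people without a job.
- **That patients without a job answer no.** This is an assumption. The case report form is not shown and may hold a not-applicable option or an employment item.
- **That the plan expressly assigns this item to a linear mixed model.** It does not. The assignment is read from one general sentence in a condensed article, and an analysis plan not shown could name another method. But that sentence is the only modelling instruction, and it makes no exception.
- **That being off work is rare.** The article gives no proportion. Few events are possible, not established.
- **That normal-theory intervals are wrong because they can fall below zero.** This applies to a single arm's proportion. The plan compares groups, and an interval for a difference may properly include negative values. Only the doubt about coverage with few events survives, and no coverage has been calculated here.
- **That the effect is diluted on every scale.** Step 2 shows the risk ratio unchanged when there are no new absences.
- **That comparing all randomised patients is invalid.** Off-work status in everyone is a legitimate intention-to-treat contrast and captures new absence, which the restricted set misses. The fault is in calling it return to work.

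**Conclusion.** The point holds in a limited form. As written, the outcome called return to work is off-work status at each visit, in a sample not selected for employment or sick leave and with no work status listed. Compared across all patients, it shrinks an absolute effect among those off work at baseline to the fraction *f* of its size: 20 points becomes 2 to 6 points for *f* of 10% to 30%. Those shares and return rates are assumptions, as is the absence of new sick leave.

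The criticism of the model is conditional. If the general sentence on linear mixed models covers every outcome, as its wording allows, it does not suit a yes/no item that may have about 3 to 4 events per arm.

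This concerns the naming, definition and analysis of one secondary outcome. It does not touch the primary outcomes of pain and disability or the sample size, and correcting it will not create useful power for return to work.

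**What to change.** 1. Record employment status alongside the item at each visit: working, off work due to back pain, or not in work.
2. Name the comparison across all patients, or across employed patients, 'off work due to back pain'.
3. Report return to work only in those off work at baseline, descriptively, as counts with exact intervals.
4. Analyse the binary item with a method suited to small counts: an exact comparison or penalised logistic regression adjusted for baseline status, or GEE if there are enough events. An ordinary logistic mixed model may fail to converge at about 3 to 4 events per arm, so it should not be the default.
5. State that the linear mixed model applies to the continuous scores.

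The cost is one more form item, a subset definition and some analysis wording. The downside is a return-to-work subset of perhaps 3 to 8 patients per arm (28 × 10% to 30%), too small for more than description.

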#### Kinesiophobia

The *Tampa Scale of Kinesophobia* (TSK) is a self-applied questionnaire consisting of 17 items, which was developed to measure the fear of movement due to cLBP. Each question has 4 response options (strongly disagree, disagree, agree, and strongly agree) with scores respectively ranging from 1 to 4 points. The scores of items 4, 8, 12 and 16 are inverted and the total score is the sum of the items, which ranges from 17 to 68 points. Increased values reflect increased fear of movement [37,38].

#### Physical activity

The *Baecke Physicial Activity Questionnaire* measures physical activity in three domains: occupational activity, physical exercises and leisure/locomotion. It consists of 16 questions structured as a quantitative *Likert* scale. Its score is determined by the sum of the domain scores. Physical activity may be classified as mild (3.0-6.7), moderate (6.8-8.1) or intense (8.2-15.0) [34].

#### Physical capacity

The sit-to-stand and 15.24 m walk tests will be used. Five repetitions of the sit-to-stand test will be performed at maximal speed, without using the hands [39]. After five minutes of rest, the walk test will be performed, in which patients walk through 7.62 m, turn around and return to the initial position. The sit-to-stand and walk test will be assessed twice with an interval of three minutes, and the average value will be used for analyses [39]. Time will be measured using a digital manual stopwatch (instrutherm®).

#### 10-repetition maximum test (10-RM)

The 10-RM test measures the maximal load that allows participants to perform 10 complete repetitions. This test will be used for the flexor and extensor muscles of the knee. The progressive method will be used, beginning with smaller loads that will be progressively increased until participants can no longer generate the torque required for completing 10 repetitions. In-between each series, individuals will rest for 1 minute.

During the first two weeks of training, individuals will exercise using 50% of the maximum load. On the third and fourth week, the load will be 60% of maximum; for the final two weeks, it will be 70% [40].

### Intervention

Interventions will last 60 minutes and will happen twice a week for 6 weeks. They will be supervised by the investigator and participants will be asked to report any complaint (adverse events) related or not to treatment. They will also be instructed not to initiate any intervention while during the study. Ongoing medications will be maintained.

#### Supervised exercise program

Patients in the Supervised Exercise Group will perform stretching, strengthening and motor control exercises, as described in Table 1.

**Table 1 T1:** Description of the protocol of the Supervised Exercise Group

**Exercise**	**Position**	**Sets/Duration**
Stretching	Stretching of the erector spinae in dorsal decubitus, with flexed hips and knees;	3 sets of 30 seconds
	Stretching of the hamstrings and triceps surae in dorsal decubitus, with forced flexion of 1 limb at a time with assistance of the physical therapist;	
	Stretching of the erector spinae with the patient sitting on heels, flexed trunk with the abdomen resting on the front of the thighs;	Intervals between series of 30 seconds
	Global stretching of the posterior muscular chain (erector spinae, hamstring, triceps surae.) 2 series of 4 minutes were performed, with 1 minute of resting interval.	
Strengthening	Exercises for the rectus abdominis in dorsal decubitus with flexed knees: trunk flexion;	2 sets of 12 repetitions
	Exercises for the rectus abdominis, external and internal obliquus in dorsal decubitus and flexed knees: trunk flexion and rotation;	
	Exercises for the rectus abdominis in dorsal decubitus and semi-flexed knees: hip flexion;	Intervals between series of 30 seconds
	Exercises for the erector spinae in ventral decubitus: trunk extension.	
Motor control	Exercises for the lumbar multifidus in ventral decubitus;	2 sets of 10 repetitions
	Exercises for the transversus abdominis muscle in dorsal decubitus with flexed knees;	
	Exercises for the transversus abdominis muscle in 4 point kneeling;	Intervals between series of 30 seconds
	Co-contraction of the transversus abdominis muscle and lumbar multifidus in the upright position.	

